## Abstract

**Introduction:** Social-distancing due to COVID-19 has led to social isolation, stress, and mental health issues in older adults, while overwhelming healthcare systems worldwide. Telehealth involving phone calls by trained volunteers is understudied and may be a low-cost, scalable, and valuable preventive tool for mental health. In this context, from patient participatory volunteer initiatives, we have adapted and developed an innovative volunteer-based telehealth intervention program for older adults (TIP-OA).

**Methods and analysis:** To evaluate TIP-OA, we are conducting a mixed-methods longitudinal observational study.

**Participants:** TIP-OA clients are older adults (age ≥ 60) recruited in Montreal, Quebec.

**Intervention:** TIP-OA volunteers make weekly friendly phone calls to seniors to check in, form connections, provide information about COVID-19, and connect clients to community resources as needed.

**Measurements:** Perceived stress, fear surrounding COVID-19, depression, and anxiety will be assessed at baseline, and at 4- and 8-weeks. Semi-structured interviews and focus groups will be conducted to assess the experiences of clients, volunteers, and stakeholders.

**Results:** As of October 15th, 2020, 150 volunteers have been trained to provide TIP-OA to 305 older clients. We will consecutively select 200 clients receiving TIP-OA for quantitative data collection, plus 16 volunteers and 8 clinicians for focus groups, and 15 volunteers, 10 stakeholders, and 25 clients for semi-structured interviews.

**Discussion:** During COVID-19, healthcare professionals' decreased availability and increased needs related to geriatric mental health are expected. If successful and scalable, volunteer-based TIP-OA may help prevent and improve mental health concerns, improve community participation, and decrease healthcare utilization.

**Clinical Trial Registration**: ClinicalTrials.gov NCT04523610; https://clinicaltrials.gov/ct2/show/NCT04523610?term=NCT04523610&draw=2&rank=1

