#### Client Referrals, Screening and Matching

Clients are either self-referred or referred from the JGH (COVID-19 inpatient units or the geriatric psychiatry clinic), long-term care facilities, local primary care clinics, or community organizations in the west-central Montreal healthcare/administrative catchment region (which represents over 500,000 residents from diverse ethnic backgrounds). Interested clients and clinicians can call our voicemail number, send an email, or fill out a form on our website to refer to our program. Included clients are consenting older adults (age ≥ 60) living in Montreal. Excluded individuals (1) are actively suicidal, (2) have a severe hearing impairment or other disability preventing the use of a phone, or (3) are suffering from moderate or severe dementia, as determined by clinical judgment (e.g., based on client history and/or past memory testing), or (4) are unable or unwilling to provide informed consent.

At intake, the screening clinician or trainee (e.g., in psychiatry, social work, psychology) spends 20–30 min on the phone with each client to collect basic demographic information and perform an informal clinical assessment regarding the client's level of cognitive functioning (coded as having suspected mild dementia or not). In cases where the client was referred from a clinic, our clinical team receives information from the referring clinician regarding the clients' cognitive and overall functioning. The screening clinician also assesses the client's level of risk and the complexity of their case, conducting a brief assessment developed primarily from Culo's paper (26) and national guidelines pertaining to seniors' mental health (27). This risk assessment is flexible and allows for the consideration of factors that are not included in the assessment, but that may hamper communication between the client and volunteer. The team then stratifies clients into categories based on case complexity and the initial risk assessment (Appendix B in Supplementary Material). Although we only assess case complexity at baseline, communication with volunteers through various channels (see section Volunteer Support and Quality Assurance) typically informs us of client mobility between categories. Following client screening and categorization, a clinician and volunteer manager assign clients to newly trained volunteers according to their assigned categories on a weekly basis.

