### Selection/Treatment of Subjects

The first 200 TIP-OA clients who provide informed consent will participate in data collection for research.

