#### Client Quantitative Outcome Measures

All primary and secondary outcomes will be assessed over the phone at baseline, 4-, and 8-weeks (primary study endpoint):

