##### Additional measures/covariates

*Baseline risk:* during the screening process, our clinician team codes clients as green (low risk), orange (medium risk), or red (high risk) (Appendix B in Supplementary Material), chiefly in order to match clients with appropriately skilled and experienced volunteers. Demographics: Age, living situation, education, mental illness diagnoses, and psychotropic medication use will be obtained at baseline. *Digital Literacy:* We will systematically measure digital literacy using the Technology in Geriatric Psychiatry scale, which is a 14-item questionnaire about patients' access to technological devices, comfort or familiarity with software, availability of family members who can assist in setting up technology, interest in learning to use video conferencing software, and interest in receiving support via videoconferencing. This scale was developed by co-investigator [name] from Harvard University and is currently being validated in another study.

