## Results—Early Experience

As of October 15th, 2020, 150 volunteers have been trained to provide TIP-OA to 305 older clients. Final research ethics approval has been provided and we will consecutively recruit 200 clients for quantitative data collection. After 8-weeks, 16 volunteers and eight clinicians will be consecutively selected for Zoom^TM^ focus groups, and 25 clients, 15 volunteers, and 10 stakeholders will be selected in the same manner for semi-structured interviews on Zoom^TM^.

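### The sampling rule does not exclude clients already receiving calls, and nothing places the outcome baseline before the first call, so the start of the pre/post comparison is not secured

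*Protocol article*

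**What the plan says.** Three places in the protocol article describe who enters the quantitative study.

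- Abstract: "We will consecutively select 200 clients receiving TIP-OA for quantitative data collection".
- Selection/Treatment of Subjects: "The first 200 TIP-OA clients who provide informed consent will participate in data collection for research".
- Results—Early Experience: by 15 October 2020, "150 volunteers have been trained to provide TIP-OA to 305 older clients". The same paragraph reports final ethics approval and continues in the future tense: "we will consecutively recruit 200 clients for quantitative data collection".

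On timing, Client Quantitative Outcome Measures gives the assessment points: "All primary and secondary outcomes will be assessed over the phone at baseline, 4-, and 8-weeks (primary study endpoint". It does not tie baseline to the first call. The Exposure section names the program as the exposure without a start point.

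Other sections point to a baseline at intake. Client Referrals, Screening and Matching uses the word for the intake coding ("Although we only assess case complexity at baseline") and puts volunteer assignment after it: "Following client screening and categorization, a clinician and volunteer manager assign clients to newly trained volunteers". Additional measures/covariates likewise places the risk code at screening: "during the screening process, our clinician team codes clients as green (low risk), orange (medium risk), or red (high risk".

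**The concern.** The Quantitative Analysis section reads the baseline and 8-week data as showing what the program does. Strengths and Limitations acknowledges that the study is observational and non-randomized. With no control arm, each client's own baseline is the only comparator, so it has to be a pre-program value.

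As written, the recruitment rule would accept a client who has been receiving calls for weeks. Four things would then go wrong for that client:

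- The Perceived Stress Scale (PSS), the primary outcome, asks about the past month, so the baseline score would partly or wholly describe life on the program.
- Mental healthcare utilization compares the eight weeks before baseline with the eight weeks after. Both windows could contain exposed time.
- The risk group, which is the between-group factor in the ANOVA, is coded once at screening and could predate the research baseline.
- The 8-week change would describe a later stretch of participation, in someone who had stayed with the program, and not the change after starting it.

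The limitations section does not mention prior exposure.

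**Working it through.** **1. The plan's own figure.** The 200 cannot be reproduced. Sample Size Justification relies on precedent and gives no effect size, SD, power or dropout. The point concerns timing, and no corrected sample size follows from it.

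**2. Can existing clients fill the places?** There were 305 clients in the program against a target of 200 (200/305 = 0.66). The existing pool could in principle supply the whole sample. This sets only an upper limit. The share p of the 200 who would already be exposed is not given and can lie anywhere from 0 to 1.

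**3. Do the sections agree on time zero?**

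| Admits exposed clients | Implies a pre-exposure baseline |
|---|---|
| Abstract: selection from clients receiving the program | Client Referrals, Screening and Matching: intake coding is called baseline, and a volunteer is assigned afterwards |
| Selection/Treatment of Subjects: first 200 to consent, with no new-client condition | Additional measures/covariates: risk coded at screening, demographics at baseline |
| Results—Early Experience: 305 in the program, 200 still to be recruited | Secondary outcomes: utilization before versus after baseline |
| Client Quantitative Outcome Measures: baseline not linked to the first call | Strengths and Limitations: risk coded at baseline, with possible movement over the 8 weeks |

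The right-hand column does not settle the matter. The intake call is described as covering demographics, cognition and risk. The PSS, COVID Fear Scale, PHQ-9 and GAD-7 are not listed there, so an intake before the calls does not by itself put the scales before them.

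**4. How much of the baseline windows would be exposed?** For a client whose first call came w weeks before research baseline, taking a month as 4 weeks:

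- PSS window: min(w, 4)/4
- Utilization window: min(w, 8)/8

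| w (assumed) | PSS window exposed | Utilization window exposed |
|---|---|---|
| 0 | 0% | 0% |
| 2 | 50% | 25% |
| 4 | 100% | 50% |
| 8 | 100% | 100% |

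**5. Effect on the measured change (illustration).** The mean change is (1 − p) × change in new clients + p × change in existing clients. If existing clients have already had a fraction f of the benefit and otherwise resemble new clients, this becomes true change × (1 − p × f). Both p and f are assumptions.

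Power uses the normal approximation for a paired change, Φ(dz × √200 × (1 − p × f) − 1.96), with assumed standardized changes dz of 0.20 and 0.30. For scale, the detectable dz at 80% power is (1.96 + 0.84)/√200 = 0.198.

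| p | f | Share of change observed | Power, dz 0.20 | Power, dz 0.30 |
|---|---|---|---|---|
| 0 | any | 100% | 0.81 | 0.99 |
| 0.5 | 0.5 | 75% | 0.56 | 0.89 |
| 1 | 0.5 | 50% | 0.29 | 0.56 |
| 1 | 1 | 0% | 0.025 | 0.025 |

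The formula ignores selection. Existing clients are those who stayed, and their later change could be smaller or larger than that of new clients.

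**The case against.** The strongest reply is that the article's own use of the word baseline points to intake, before any call. The risk code is called a baseline item, demographics are collected at intake and also listed as baseline items, volunteers are assigned after screening, and the utilization comparison makes sense only with a pre-exposure baseline. The limitations section treats the risk code and the 8-week follow-up as starting together. The analysis section also reports past experience with incomplete baseline questionnaires, which suggests that baseline collection was already under way. The Abstract's phrase may be only a label for the program's population, and consecutive recruitment could mean consecutive new intakes. Finally, the full protocol is not shown and may fix the order of consent, scales and first call.

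Much of this stands. A reader might infer that the 200 are in fact drawn from people already receiving calls, and that the change from baseline therefore cannot measure the effect of starting. The documents do not support that: nowhere are the 305 named as the sampling frame, and p may be 0. Nor do they support a specific loss such as 25% to 50%, which only restates assumed inputs.

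The reply does not remove the conflict. This is more than an unreported detail, because the article states an entry rule, and that rule admits clients whose data cannot serve the before/after comparison implied elsewhere. The remark about past baseline data gives no timing relative to the first call.

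**Conclusion.** The concern holds as an unresolved conflict over time zero. The stated entry rule does not exclude clients already receiving calls, and no sentence requires the outcome scales before the first call, while other sections presuppose that they come first. If exposed clients enter, the baseline-to-8-week change mixes change after starting with change later in the program.

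The size cannot be determined from the documents. It is nil if every baseline precedes the first call. Under the illustrative model it reaches complete loss only if all 200 are existing clients who have already had their full benefit. The direction is also uncertain, because prior benefit would shrink the change while selection of those who stayed could move it either way.

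The absence of a control group is a separate limitation. The article acknowledges the non-randomized, observational design, and correct baseline timing would not make the change a causal estimate.

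**What to change.** Reconcile the Abstract, Selection/Treatment of Subjects and Results—Early Experience with Client Referrals, Screening and Matching, Client Quantitative Outcome Measures and Secondary outcomes:

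- State in Selection/Treatment of Subjects that consent and all baseline scales are completed before the first volunteer call, and that only such new clients count toward the 200 in the primary PSS analysis.
- Record the date of each client's first call, so that the order can be checked.
- If existing clients are enrolled, report them separately, with time since first call.
- If baseline has in fact always been taken before the first call, say so and reword the Abstract to match.

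The cost is one or two sentences and one date field. Accrual would be somewhat slower, because clients already in the program would not count toward the primary sample.

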## Introduction

The novel SARS-CoV-2 virus causing COVID-19 emerged in late 2019 (1) and has resulted in 9,660 deaths in Canada and 1.09 million globally as of October 2020 (2). Older adults are overrepresented in the mortality rates, largely due to the higher prevalence of comorbidities and lower immunity seen in this population (3, 4). Globally there are 4.5 billion people in voluntary confinement, including in Canada where the government has urged individuals over the age of 70 to stay at home for the foreseeable future (5). Due to COVID-19 government regulations, community- and residence-dwelling older adults in Montreal are more home-bound; consequently, they may have fewer social interactions or feel more isolated, potentially increasing the risk of stress, depression, anxiety, cognitive decline, and re-hospitalization (6–8). Prior to the pandemic, mental health conditions affected more than 10–15% of older adults (>1,000,000 Canadians) with estimated costs of $15 billion/year (9, 10). The increased vulnerability of the geriatric population during COVID-19 may result in elevated mental health demands, which would further overwhelm the healthcare system (11).

A proposed means of increasing access to mental healthcare during COVID-19 is through telehealth, or the use of technology for remote clinical care and health education (12). Telehealth is a promising avenue for improving symptoms of depression (13) and anxiety (14), and has also been used to connect with socially isolated older adults (12, 15). In one pre-COVID-19 telephoning initiative, older adults formed satisfying relationships, gained confidence, engaged with their community, and became more socially active (15). However, as highlighted by Noone et al., there is a lack of conclusive evidence regarding the effectiveness of video call interventions for reducing loneliness and depression in seniors (16). There is thus a need for more rigorous research with diverse samples to discern whether increased social interaction with volunteers via telephone has the potential to improve psychological outcomes such as symptoms of depression or anxiety.

Currently, global healthcare systems are overburdened, with professionals increasingly becoming burnt out, reassigned, or infected (17, 18). Additionally, most experts agree that a second wave of infection will occur in the fall of 2020 (19), thus implementing community-based volunteer interventions could aid current mental health support services by preventing the development or worsening of mental health issues. For example, in India, a successful mental health intervention with lay volunteers improved depression and other psychiatric symptoms in older adults by providing problem-solving strategies, health education, and assistance in accessing medical and social programs (20). Indeed, not all telehealth modalities may be accessible to older adults (21); one survey found that only 10% used the internet, while 72% owned a cell phone (22). In the context of COVID-19, many telehealth interventions requiring advanced digital literacy are likely unfeasible for rapid implementation due to a lack of infrastructure, training, and low rates of digital literacy in older adults (23). Given these limitations, telephone-based care is likely able to serve the largest proportion of older adults. Thus, we have started a novel volunteer-based telehealth intervention program for older adults (TIP-OA) in Montreal, Canada. The objective of the study is to assess the efficacy of this program by:

Evaluating the effects on perceived stress, fear related to COVID-19, symptoms of depression and anxiety in older adults (i.e., clients), as well as the effects on mental healthcare utilization.Comparing clients' mental health outcomes based on baseline risk (i.e., low, medium, or high risk).Analyzing the experiences of clients, clinicians, volunteers, and organizers/stakeholders involved in the program using semi-structured interviews and focus groups.

## Methods and Analysis

### Design

We are offering a large-scale telehealth intervention program, whereby trained volunteers make weekly friendly phone calls to older adults in Montreal, Canada to serve three main purposes:

To provide friendly conversation and social connection;To provide information about COVID-19;To connect older adults with services and resources in the community to ensure that the necessities of daily living (e.g., food, shelter, medication, etc.) are met.

The program is a community-based social support intervention that may serve both as prevention and treatment of mental health issues in older adults. In order to evaluate the program and share our findings internationally, we are also conducting a mixed-methods longitudinal study. We are consecutively sampling clients, volunteers, and other implicated parties and collecting both quantitative and qualitative data to understand the impact of this intervention.

#### Telehealth Intervention Program for Older Adults (TIP-OA)

#### Recruitment and Training of Volunteers

Volunteers are recruited (1) using an advertisement circulated on social media; (2) through direct recruitment of medical, social work, psychology, and nursing students from McGill University; (3) from the research and clinical teams' social networks; and (4) through the Jewish General Hospital (JGH) Foundation and Auxiliary, a volunteer non-profit organization. Interested individuals are rigorously screened and interviewed using Zoom^TM^, a widely used video conferencing platform. Selected inclusion criteria are the ability to (1) commit for a minimum of 3-months; (2) provide this service to 3-5 clients; and (3) call each client at least once every week. Applicants with a criminal record or applicants who refuse to submit to a background check are excluded from volunteering.

Members of the volunteer management team stratify volunteers according to past volunteering and clinical experience(s) (Appendix A in Supplementary Material). Two trainers facilitate two weekly 2-h training sessions over Zoom^TM^, to a maximum of five volunteers per session (please contact [contact] for more information regarding the training design and/or manual). The initial virtual training was provided in kind collaboration with the Touch-Volunteers in Partnership (ViP) program at the Jewish General Hospital. The Touch ViP program was created through a participatory mixed-methods study, which engaged persons living with mental health conditions, their families, and mental health professionals over 3 years to support recovery-oriented practices (24, 25). The Touch Volunteer Manual, originally designed for in-patient services, was adapted for telehealth and is provided to TIP-OA through the *What connects us-Ce qui nous lie project* Dementia Community Investment fund (1920-HQ-000092), to support the aim to create a web of inter-sectoral resources and decrease stigma. In addition to the stratified matching, the program has been further modified for TIP-OA to address the needs of older adults during COVID-19 with feedback from trainers, clinicians, and volunteers.

The volunteer training covers topics such as client consent, confidentiality, active listening, responding to possible suicide risk, community resources (e.g., grocery delivery and hotline services), and common scenarios that may come up during calls. The training also includes basic information about psychotic features and instructs volunteers to reach out to the clinical team if they require extra support in interacting with their client, or if they have concern for the safety and well-being of their client or someone else. The design of this training informs the follow-up methodology used to support volunteers, with an emphasis on stigma reduction as a means toward interpersonal connection. Similar to Touch, the training and implementation are iterative and responsive to the needs of volunteers and clients.

#### Client Referrals, Screening and Matching

Clients are either self-referred or referred from the JGH (COVID-19 inpatient units or the geriatric psychiatry clinic), long-term care facilities, local primary care clinics, or community organizations in the west-central Montreal healthcare/administrative catchment region (which represents over 500,000 residents from diverse ethnic backgrounds). Interested clients and clinicians can call our voicemail number, send an email, or fill out a form on our website to refer to our program. Included clients are consenting older adults (age ≥ 60) living in Montreal. Excluded individuals (1) are actively suicidal, (2) have a severe hearing impairment or other disability preventing the use of a phone, or (3) are suffering from moderate or severe dementia, as determined by clinical judgment (e.g., based on client history and/or past memory testing), or (4) are unable or unwilling to provide informed consent.

At intake, the screening clinician or trainee (e.g., in psychiatry, social work, psychology) spends 20–30 min on the phone with each client to collect basic demographic information and perform an informal clinical assessment regarding the client's level of cognitive functioning (coded as having suspected mild dementia or not). In cases where the client was referred from a clinic, our clinical team receives information from the referring clinician regarding the clients' cognitive and overall functioning. The screening clinician also assesses the client's level of risk and the complexity of their case, conducting a brief assessment developed primarily from Culo's paper (26) and national guidelines pertaining to seniors' mental health (27). This risk assessment is flexible and allows for the consideration of factors that are not included in the assessment, but that may hamper communication between the client and volunteer. The team then stratifies clients into categories based on case complexity and the initial risk assessment (Appendix B in Supplementary Material). Although we only assess case complexity at baseline, communication with volunteers through various channels (see section Volunteer Support and Quality Assurance) typically informs us of client mobility between categories. Following client screening and categorization, a clinician and volunteer manager assign clients to newly trained volunteers according to their assigned categories on a weekly basis.

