#### Exposure

The client exposure for the quantitative portion of this study is the TIP-OA intervention.

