##### Secondary outcomes

*The COVID Fear Scale* is an 18-item scale measuring individuals' anxiety, fear, and concern surrounding the COVID-19 pandemic. Items include: “Fear that I will be infected” and “Worry if I will be assigned to COVID wards if hospitalized” (29). The *Patient Health Questionnaire-9 (PHQ-9)* is a 9-item self-report questionnaire used to assess depressive symptom severity. The questionnaire asks individuals how often in the last 2 weeks they have been bothered by problems like “feeling down, depressed, and hopeless” and “poor appetite or overeating.” Scores for each question include 0 (not at all), 1 (several days), 2 (more than half of the days), and 3 (nearly every day) (30). The *Generalized Anxiety Disorder 7-Item Scale (GAD-7)* is a brief scale that measures symptoms of anxiety present in the previous 2 weeks. Respondents' scores can range from 0 (not at all sure) to 3 (nearly every day). Items include “Not being able to stop or control worrying” and “Being so restless that it's hard to sit still” (31). *Mental healthcare utilization* will be assessed using medical records, including the number of ER visits, hospitalizations, and outpatient visits (1) in the 8 weeks prior to baseline and (2) during 8-week follow-up.

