### Data Analysis

#### Quantitative Analysis

Descriptive statistics for continuous variables will include means and standard deviations, while categorical variables will be summarized using frequencies and proportions. A within-subjects repeated measure analysis of variance (ANOVA) will be conducted for the PSS (primary outcome), COVID Fear Scale, PHQ-9, GAD-7, and mental healthcare utilization (secondary outcomes) to assess differences in measures between baseline and the 8-week follow-up between groups with different baseline risk (low, medium, and high risk). Additional analysis of covariance (ANCOVAs) will control for variables that differ between groups at baseline. We will use LOCF to handle missing data that results from study attrition. Although we have found it extremely rare to be missing baseline data when, for example, a participant answers all but one question on a measure, in any such case we will exclude the participant's data for that measure. All ANOVAS will be tested at two-tailed alpha = 0.05. Linear mixed effect regression models, adjusting for age and sex, will analyze the effect of TIP-OA on all outcomes (PSS, COVID Fear Scale, PHQ-9, GAD-7, and mental healthcare utilization) collected at baseline and 8-week follow-up. We will perform additional linear mixed effect regression models accounting for a larger group of important variables such as client referral source (e.g., referred from clinic vs. self-referred) and cognitive functioning (e.g., suspected mild dementia vs. no suspected mild dementia) on mental health outcomes. Variable selection in linear mixed effect model (32) will be used to select important fixed effect covariates as they relate to the outcome. The fixed effect point estimates and corresponding confidence intervals and *p*-values will be computed. Additional subgroup analyses will also compare the primary outcome (PSS) between important subgroups [e.g., referral source (referred from clinic vs. self-referred) and cognitive functioning (suspected mild dementia vs. no suspected mild dementia)]. Analyses will be run using R statistical software.

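### The described analysis cannot separate natural recovery in clients referred from COVID-19 inpatient units from the effect of the program

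*Protocol article*

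**What the plan says.** All references are to the protocol article.

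- **Client Referrals, Screening and Matching** lists the sources: "Clients are either self-referred or referred from the JGH (COVID-19 inpatient units or the geriatric psychiatry clinic"), together with long-term care, primary care and community organizations. With self-referral that makes six routes. Eligibility is broad: "Included clients are consenting older adults (age ≥ 60) living in Montreal". The exclusions are active suicidality, inability to use a phone, dementia (those who "are suffering from moderate or severe dementia, as determined by clinical judgment") and lack of consent. None concerns recent acute COVID-19 or a current hospital stay.
- **Exposure** defines one exposure and no comparator: "The client exposure for the quantitative portion of this study is the TIP-OA intervention".
- **Client Quantitative Outcome Measures** places assessments at baseline, 4 weeks and 8 weeks, by phone. Baseline is not tied to the date of illness or discharge.
- **Primary outcome** and **Secondary outcomes** give a past-month recall window for the PSS and two weeks for the PHQ-9 and GAD-7. The PHQ-9 includes "poor appetite or overeating". The 18-item COVID Fear Scale includes "Worry if I will be assigned to COVID wards if hospitalized" and an item on fear of becoming infected.
- **Quantitative Analysis** uses mixed models adjusted for age and sex to estimate the program's effect from baseline and week-8 data. Further models account for "client referral source (e.g., referred from clinic vs. self-referred") and cognitive functioning. A subgroup comparison by referral source is planned for the PSS. No interaction of referral source with time is stated.
- **Strengths and Limitations** names the non-blinded, non-randomized, observational design as the main limitation. It does not mention natural recovery.

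**The concern.** A client referred from a COVID-19 inpatient unit may answer the baseline questionnaires while the recall window still covers the illness or the admission. At week 8 the PSS looks back over roughly weeks 4 to 8 and the PHQ-9 over weeks 6 to 8, so an illness that ended by baseline lies outside both windows. If stress, appetite or mood recover in between, scores fall without any help from the calls. A single-cohort before-after analysis has nothing to set against that fall and counts it as benefit.

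Most weaknesses of an uncontrolled design cannot be examined in the study's own data. This one can, because it sits in a group that the referral record identifies. The described analysis does not single that group out. What is at stake is whether a significant mean change at week 8 could partly reflect convalescence.

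**Working it through.** **The plan's own figure.** The article sets 200 clients but gives no power, effect size or SD (Sample Size Justification rests on comparable studies), so 200 cannot be reproduced. It serves below only as n, with the stated two-tailed alpha of 0.05.

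**Why a main effect does not help.** Suppose the program has no effect, a share f of clients comes from COVID-19 units, and those clients improve naturally by r. With complete data at baseline and week 8, the time coefficient is the mean within-client change:

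f × r + (1 − f) × 0 = f·r.

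A main effect of referral source shifts a client's level equally at both visits and cancels from the within-client change. The time coefficient stays at f·r. A clinic versus self-referred split, even with an interaction, leaves these clients inside whichever level they are assigned to. Only a separate level with its own interaction with time, or an analysis without them, takes f·r out.

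**What n = 200 can detect.** In units of the SD of change, the detectable shift at 80% power is (1.960 + 0.842)/√200 = 0.198. The shift that just reaches significance is 1.960/√200 = 0.139.

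**Chance of p < 0.05 from recovery alone.** Assumed inputs are the share f and the recovery s in SDs of change, with other clients unchanged. The pooled shift is f·s. The pooled SD is √(1 + f(1 − f)s²). The test uses a two-sided normal approximation for a paired change.

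Example, f = 20% and s = 0.8: shift 0.16; SD √(1 + 0.16 × 0.64) = 1.050; expected z = (0.16/1.050) × √200 = 2.155; chance 57.7%.

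| Share f | Recovery s | Pooled shift (SD) | Chance of p < 0.05 |
|---|---|---|---|
| 2% | 0.5 | 0.010 | 5.2% |
| 5% | 0.5 | 0.025 | 6.4% |
| 10% | 0.5 | 0.050 | 10.8% |
| 10% | 1.0 | 0.100 | 27.3% |
| 20% | 0.5 | 0.100 | 28.4% |
| 20% | 0.8 | 0.160 | 57.7% |
| 20% | 1.0 | 0.200 | 74.7% |
| 30% | 0.8 | 0.240 | 89.0% |

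For recovery alone to equal the 0.198 SD detectable at 80% power, the share must be 0.198/s: about 20% at s = 1.0, 25% at 0.8, 40% at 0.5 and 66% at 0.3.

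**The same in PHQ-9 points.** Assume a 4-point recovery and an SD of change of 5 (s = 0.8). The pooled fall is 4f: 0.4 points at 10%, 1.0 at 25%. SE = 5/√200 = 0.354; 1.96 × 0.354 = 0.693; 0.693/4 = 17.3%. At that share the expected result sits on the significance boundary, so about half of such studies would give p < 0.05. Allowing for the larger pooled SD moves the share to about 18%. With a 2-point recovery it is 0.693/2 = 34.7%.

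**The case against.** The strongest reply has four parts.

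*Timing.* A reader might infer that these clients are measured during or just after acute COVID-19. The article does not say so. It names the units only as a referral source and leaves the interval to baseline open. This stands: a baseline near the illness is possible, not established.

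*Direction.* A reader might infer that every scale would fall. For the COVID Fear Scale this does not follow. Items about becoming infected or being placed on a COVID ward may mean something different to people already hospitalized with the disease, and their fear could start low and rise. For the PSS the support is its recall window alone. For the PHQ-9 it is the recall window and an appetite item. A reader might also infer that the COVID-19 admission inflates the pre-baseline utilization count. That outcome is labelled mental healthcare, and the text does not say whether such an admission counts, so nothing here rests on it.

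*Size.* Share, recovery and SD are all assumed, and COVID-19 units are one of six routes. Shares of a few per cent are plausible and would make the bias negligible. This stands. Nor does a 17% share guarantee a significant result.

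*Coverage.* Referral source is already in the additional models and the PSS subgroup comparison, the clinic versus self-referred split is only an example, and the observational design is admitted. The subgroup comparison could reveal the problem for the PSS if these units were a separate level. But it is stated for the PSS only, the illustrated split does not name them, and a main effect leaves recovery in the time effect. The admitted limitation is general and changes no analysis.

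**Conclusion.** The point holds as a conditional one. Clients from COVID-19 inpatient units may have baselines near acute illness, and the analysis as described has no stated means of keeping their natural recovery out of the estimate attributed to the program. Whether that matters depends on a share that the article does not report. At about 2–5% with a recovery of 0.5 SD it is negligible. It is material only at about 20% or more with a moderate to large recovery. The calculations assume no program effect, no change in other clients and a normal approximation at n = 200. For the PSS and PHQ-9 the expected direction is towards benefit, but this is not certain. For the COVID Fear Scale no direction can be given. The documents do not support the stronger statement that recovery will be counted as improvement, nor that the primary result is invalid.

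**What to change.** In Quantitative Analysis:

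1. Code the COVID-19 inpatient unit as its own level of referral source.
2. Include the interaction of that level with time in the mixed models, and keep it in whatever the planned variable selection returns.
3. Report how many clients come from this source.
4. Report change in PSS, PHQ-9, GAD-7 and COVID Fear Scale with and without these clients, as a prespecified sensitivity analysis, and state in the conclusion whether the result holds without them.

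The conclusion need not rest solely on the analysis without them, since the study aims for a heterogeneous sample. If the group is small, the interaction will be imprecise and the comparison with and without these clients will carry most of the information.

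The cost is a few lines of analysis text, since referral source is already an analysis variable, and slightly lower precision in the analysis without them. The change does not remove the other limits of having no control group, including natural improvement in clients from other sources.
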